## Abstract

**Background:**

Falls amongst people with Parkinson’s (PwP) result in significant disability and reduced quality of life. There is emerging evidence that exercise-based and physiotherapeutic interventions are of benefit for improving fall risk factors, such as balance. However, the benefit, in terms of preventing falls, is mixed. The development of effective interventions has been identified as the highest research priority for this population.

The aim of this trial is to establish the effectiveness and cost-effectiveness of a novel, home-based physiotherapy programme, compared with usual care, on falls amongst PwP.

**Methods/Design:**

A UK multi-centre, community-based, single blind, randomised controlled trial with twelve month follow-up, and nested economic evaluation and qualitative studies will be undertaken. Six hundred PwP who live in their own home, have had one or more falls in the previous year and an MMSE score of ≥24 will be recruited. Those living in care homes and those needing assistance from another person to walk indoors will not be eligible.

The intervention is a physiotherapist delivered, individually tailored and progressive, home-based programme (PDSAFE) comprising task orientated movement strategy training, functional lower limb strengthening and balance training, of six months duration. Unsupervised daily home exercises and strategies will be practised and supported using technology. Control participants will receive usual care.

Data collection will include falls, cognitive state, balance and mobility, fear of falling, freezing of gait, mood, quality of life, carer quality of life and resource use. Data will be collected at baseline, three, six and twelve months. Longitudinal semi-structured interviews will be undertaken with forty participants to explore the expectations and experiences of participants.

The primary outcome is risk of repeat falling at six months post-randomisation.

**Discussion:**

The aims of this trial are to establish the effectiveness and cost-effectiveness of a novel, home-delivered physiotherapy intervention (PDSAFE) compared with usual care on risk of falling for PwP who have a history of falling. PDSAFE is a novel intervention that builds upon the existing literature and targeting known risk factors, being the first study that uses a novel delivery modus (technology) in conjunction with traditional physiotherapeutic approaches.

**Trial registration:**

Current Controlled Trials ISRCTN48152791

## Background

In the UK, there are estimated to be around 127,000 people with Parkinson’s (PwP) [1]. The lifetime prevalence of Parkinson’s in the UK is two per thousand with an annual incidence of nineteen per hundred thousand population [2]. PwP are twice as likely to experience falls when compared with the community-dwelling, older population due to both physical and cognitive impairments [3]. Falls and fall-related injuries have not been identified separately within cost of illness studies in Parkinson’s [4] but contribute to morbidity, hospital admissions and reduced quality of life in this population [5,6]. A national survey among the national Parkinson’s Foundation Centres in the USA listed falls and fractures as one of the top reasons for hospitalisation in this population [7]. Similarly, an Australian study reviewed 645 admissions in which Parkinson’s was a secondary diagnosis and identified falls and related fractures as the leading reason for hospitalisation accounting for 13% of the total cases [8]. A recent survey of a thousand PwP, carers, and health and social care professionals reported the development of interventions to reduce falls and improve balance as the highest research priority [9].

A UK survey involving over 13,000 PwP indicated that only 54% had ever seen a physiotherapist as part of their management [10]. The prevention of a cycle of inactivity and injurious falls is a global priority [11]. Despite a wealth of evidence of effective interventions, in particular exercise, for reducing falls in the general older population [12,13], the evidence to date for the prevention of falls for PwP is mixed [14]. People with reduced balance control and falls respond poorly to medication, the mainstay of Parkinson’s management [15]. In a randomised controlled trial of home-based physiotherapy with 142 participants, Ashburn et al. [16] demonstrated a non-significant difference in fall risk at six months of −5% (95 % CI −20 %, 10 %). Goodwin and colleagues [17] compared a physiotherapist-led group strength and balance programme plus additional home-based exercises with usual care and reported a fall incident rate ratio (IRR) of 0.74 (95 % CI 0.41, 1.33) at 20 weeks. A recently published trial from Australia evaluating an intervention that comprised progressive strength and balance training and cueing strategies for six months also reported a non-significant reduction in falls, however subgroup analysis indicated the programme was effective for those with lower disease severity [18]. An RCT of Tai Chi for those with mild Parkinson’s was effective at reducing falls as a secondary outcome [19]. Despite the limited evidence for reducing falls, there is evidence of the benefit of exercise on fall risk factors, such as impaired balance [20] and of movement strategies to reduce freezing [21]. There is also a high probability of exercise interventions being cost-effective for PwP [22].

PwP have different risk factors for falling than the general older population, including freezing of gait, cognitive impairment and poor mobility [23]. A recent paper [24] reported that ambulatory activity and the context in which people fall contributes to the heterogeneous nature of falls in PwP and that “one size fits all” interventions are unlikely to be beneficial. Interventions therefore need to be multimodal and individually tailored in order to be effective.

The aim of this trial is to establish the effectiveness and cost-effectiveness of a novel, home-based physiotherapy programme called PDSAFE, compared with usual care, on falls amongst PwP. A nested longitudinal qualitative study additionally seeks to explore the views, expectations and experiences of trial participants, in order to further explain findings of the trial.

## Methods/Design

### Trial design and setting

The trial is a UK multi-centre, community-based, single blind, randomised controlled trial with twelve month follow-up, with nested economic evaluation and qualitative studies. The trial will be conducted at four sites: Southampton, Portsmouth, Bournemouth /Poole and Exeter. The primary outcome is risk of repeat falling over the 6 month period. Ethical approval has been given by the National Research Ethics Service - South Central – Hampshire B (Reference 14/SC/0039). Trial registration reference is ISRCTN48152791.

### Participants

Participants will be eligible for the trial if they: (a) have a confirmed consultant diagnosis of Parkinson’s; (b) live at home; (c) have had one or more falls in the previous year; (d) score ≥24 of the Mini-Mental State Examination (MMSE) [25]; (e) are able to understand and follow instructions; (f) are able to undertake an exercise programme; (g) are able to give informed consent. Exclusion criteria are: (a) living in a care home; (b) need assistance from another person to walk indoors; or (c) wheelchair bound or bedridden unless aided as defined by Hoehn and Yahr Stage 5 [26].

### Sample size

The primary outcome is the risk of repeat falling between 0–6 months. In a previous trial of PwP with two or more falls in the previous year [16], the risk of repeat falling at six months was 68 % (42/63) for controls versus 56 % (35/63) in the exercise group. However, the population in the proposed trial will include those with one or more previous falls and we therefore anticipate the risk of repeat falling to be lower. Assuming a control group risk of repeat falling between 0–6 months to be 63 %, and 50 % in the intervention group, a sample size of 228 participants per group (n = 456 total) with data for analysis is indicated. Allowing for 10% drop out between agreeing to the 3 months pre-randomisation fall data collection and randomisation, and 5 % of loss to follow-up at 6 months amongst those randomised, a total of 534 participants need to be recruited. We aim to recruit 600 participants. Figure 1 provides a flow diagram showing anticipated numbers at recruitment and follow-up.

**Figure 1 Fig1:**
[figure not shown]
Trial flow diagram

### Recruitment

Potential participants will be identified from clinical registers of PD specialists at each site, research registers of those who have previously indicated interest in taking part in future research, and from Parkinson’s UK local groups, supported by the National Institute for Health Research (NIHR) Clinical Research Network (CRN). Those identified from clinical registers will be invited to participate, in writing, by their specialist, and those expressing an interest will be asked for permission to pass their contact details onto the research team in order that further information can be shared, and the opportunity to participate offered. All potential participants will be provided with a Participant Information Sheet, a reply slip and pre-paid envelope. On receipt, those expressing interest will be contacted by telephone by the research team to confirm eligibility and offered a home visit (allowing at least 24 hours for consideration before proceeding) to gain written informed consent and complete screening measures. Once consent is gained, demographic data, medical history, MMSE, Montreal Cognitive Assessment (MoCA) [27], Hoehn & Yahr score and number of falls in previous year will be collected and participants will be given diaries to complete for three months to prospectively record any fall events. Permission at this time will also be sought to pass details of those randomised to the intervention arm to a qualitative researcher in order that contact can be made to discuss involvement within the nested qualitative study (see below). Where appropriate, carers will also be invited to participate in the study and will be provided with a carer information sheet. Recruitment commenced in July 2014.

### Randomisation

Following baseline assessment, individuals will be randomised in a 1:1 ratio to either intervention or control arms, stratified by site, using random block size of 2, 4, 6 or 8 to ensure balance within each site, whilst maintaining allocation concealment. The aim will be to undertake the randomisation between thirteen and sixteen weeks post baseline assessment after the completion of three months of pre-randomisation fall diaries. The process will be coordinated by the UKCRC registered Oxford Clinical Trials Unit. To ensure concealment, study allocation will be undertaken using a password protected, web-based portal with allocation only generated after registration of each eligible participants. Randomisation outcome will be e-mailed to the trial co-ordinating centre and the details of allocation will be forwarded to the physiotherapy team who will advise on the timescale for their first visit which should be within two weeks (maximum of four weeks).

### Interventions

All trial participants will continue to receive usual care as deemed by their care providers, including medical and nurse specialist assessment and interventions, such as medication management, as well as usual activities, such as exercise or social groups. They will be encouraged to avoid changing their activity unless specifically advised by a healthcare professional, as well as keep a record of their usual care and activity and any exercise classes outside of the trial for the duration of the study.

The central component of the PDSAFE intervention is a physiotherapist delivered, individually tailored, progressive home-based exercise programme to target modifiable risk factors for falls, including freezing, balance and mobility impairment and physical activity. The programme was informed by the following work – The FaME programme [28], the EXSart Trial [16], the Otago Exercise Programme [29], the PD-WEBB programme [18], the GETuP trial [17], David et al. [30], Mayer et al. [31] and the American College of Sports Medicine [32]. The programme will be delivered by physiotherapists who will undertake an assessment to identify impairments and activities that will be addressed within the intervention programme. The programme will comprise a warm up session and three main active elements:Warm up and major muscle group stretches to prepare the body for exercise and enable the body to move more freely when exercising.Task-orientated movement strategy training to improve freezing of gait and performance of complex tasks specific to fall-related activities and circumstances within the home environment. A context and task specific evaluation of falls risk will be undertaken to identify specific problematic areas and strategies identified to address the problems. Videos will be recorded by the therapist using a tablet of the participant engaged in activities with and without the use of strategies. Training will include activities such as turning, and single and dual tasks of complex functional activities. Tailored video vignettes of strategies will be given to participants on a DVD to remind and reinforce between face-to-face sessions. This type of technology has been shown to be of benefit for delivering fall prevention exercises [33]. Participants will be asked to practice the strategies daily and to integrate these into daily functional tasks where possible.Functional lower limb strengthening exercises will be progressive using bodyweight or a weighted vest, maintaining intensity at a moderate-hard level as assessed by the Borg Scale (Borg 1987).Dynamic balance exercises will be progressed through more complex activities and varied starting positions, postures and cognitive challenges maintaining difficulty at a moderate to hard level.

An individualised booklet of exercises will be provided, selected from a menu following assessment. If an individual struggles in achieving a good technique the physiotherapist will video record them doing the exercises correctly using a tablet device. This recording will be shared with the participant to provide them with an accurate visual reference when practising. Participants will be encouraged to perform all exercise components daily. However, to avoid the possibility of overload, a daily safety questionnaire is completed, that advises participants which components to complete and which to leave, due to the risk of fatigue or other safety issues.

The intervention will take place over a six-month period and will consist of up to twelve, one hour face-to-face sessions with the physiotherapist. These face-to-face sessions will be delivered more intensely to start but less frequently over time to maximise motivation and promote independence. The exact delivery of these, however, will be negotiated between the physiotherapist and participant. This model of delivery is unique in exercise studies for PwP. An example delivery model could be:Twice a week for weeks 1–2Once a week on week 3, 4, and 5Once a month at 2, 3, 4, 5 and 6 months.

Participants in the control group will continue to receive usual care and will be advised to continue any activities in which they usually participate, but not to commence new activities, if possible. In addition, they will be visited once by a physiotherapist within four weeks of completing pre-randomisation fall diaries and provided with a DVD about Parkinson’s. After the twelve month follow-up assessment has been completed, they will receive written and verbal guidance on physical activity and strategies by the physiotherapist.

### Physiotherapist training

Physiotherapists will deliver the intervention in participants’ homes across the four study centres. In order to minimise inter-therapist variation and enhance fidelity, a detailed training programme has been developed that includes clinical reasoning for prescribing the exercises and strategies and practical delivery of the programme. This is delivered in a two-day face-to-face session. Once trained and delivering the intervention there will be regular team meetings including masterclass sessions, case studies, and weekly telephone support from the lead physiotherapist.

### Data collection

#### Pre-randomisation fall data

Participants will be asked to prospectively record falls using a monthly diary for the three months between recruitment and randomisation. This process will enable participants to become familiar with the procedure for recording falls and assist the research team with identifying those participants who may need additional support to complete the diaries. In addition, the data will be used in the main trial analysis as a covariate.

### Baseline assessment

On completion of three months of pre-randomisation fall data, an assessor will visit the participants (and carer) at home to complete baseline data collection (Table 1) comprising functional activities, Parkinson’s severity, freezing, quality of life, depression, fear of falling and physical activity. Information about current medication, social status and rehabilitation input will also be collected. This assessment will be undertaken prior to randomisation and the assessor will be blinded to subsequent allocation.

**Table 1 Tab1:** Data Collection

	Method	Screening (3 months pre-baseline)	Baseline	3 months	6 months	12 months
MMSE [25]	Researcher assessed	x				
Hoehn and Yahr Scale [26]		x				
MoCA [27]		x				
Mini BesTest [53]			x	x	x	x
Timed Chair Stand [54]			x	x	x	x
MDS-Unified Parkinson’s Disease Rating Scale (UPDRS) - motor scale [55]			x	x	x	x
Falls Efficacy Scale International [56]	Self-report (face-to-face)		x	x	x	x
EuroQoL (EQ-5D) [37]			x	x	x	x
New Freezing of gait questionnaire [57]			x	x	x	x
Parkinson’s Disease Questionnaire 39 [58]			x	x	x	x
Physical Activity Scale for the Elderly [59]			x	x	x	x
Geriatrics Depression Scale [60]			x	x	x	x
Carer Experience Scale (CES) [38]			x	x	x	x
Carer Strain Index (CSI) [39]			x	x	x	x
Health and Social Care resource use			x	x	x	x
Falls, near falls, fractures		x				
Adverse events		x				

### Follow-up assessment

Follow up data (Table 1) will be collected at three, six and twelve months post-randomisation during a face-to-face visit to the participants’ home by an assessor blinded to group allocation. Serious adverse events (SAE) have been defined as hospitalisation as a result of a fall directly linked to the treatment with a therapist or whilst doing it on their own. Previous experience within the team suggests that participants may inadvertently unblind assessors. We aim to minimise this through explicit reminders prior to assessment visits. We will also ask assessors to record their estimate of which study arm they believe participants have been allocated to, and their confidence in that belief at the end of the trial. This will enable us to examine the extent of unblinding. Assessments will last approximately 90 minutes and, where possible, all assessments for an individual will be arranged for a similar time of day at mid-medication cycle when movement is optimal.

Fall data will be collected using monthly, prospective, self-report diaries for twelve months following randomisation and will include falls, near falls and injuries [34]. In addition to the diary, participants will be provided forms to completed details of any falls such as location and subsequent treatment [35]. The diaries will be delivered by the assessor at assessment visits and returned each month in a pre-paid envelope and with telephone reminders when not received within three weeks.

The implementation of the intervention protocol in terms of quality and dose will be monitored [36]. Joint patient sessions will be undertaken with the lead physiotherapist to assess intervention fidelity. Participant adherence to the unsupervised programme will be established by them completing a daily tick sheet of the exercises they have completed.

For the economic evaluation, resource use (health and social care) and carer data will be collected using a tick box resource sheet aided by a resource use diary. Additional resource use will be collected within the fall dairies. Information on hospital admissions, length of stay, ambulance call outs, A&E attendances, GP and specialist appointments, physiotherapy, occupational therapy and admission to a care home will be identified and measured. Costs of implementing PDSAFE include training, time to deliver the intervention (face-to-face and telephone), travel, equipment and DVD production will also be identified and measured. Participant quality of life (QOL) data will be collected using the EuroQOL EQ-5D instrument [37] during assessment visits to enable the measurement of Quality Adjusted Life Years (QALYs). To capture any potential spillover QOL impacts carer data will collected using the Carer Experience Scale (CES) [38] and the Caregiver Strain Index (CSI) [39].

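### The blinded assessor's follow-up visit includes resource use, with physiotherapy among its items, so a required question can reveal allocation to the person scoring the rated secondary outcomes

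*Protocol article*

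**What the plan says.** All references are to the Protocol article.

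- **Who collects, and when** (Follow-up assessment): "Follow up data (Table 1) will be collected at three, six and twelve months post-randomisation", and this is done "during a face-to-face visit to the participants’ home by an assessor blinded to group allocation".
- **What is collected** (Baseline assessment, Table 1): the row "Health and Social Care resource use" is marked at baseline, 3, 6 and 12 months. The Mini BesTest, timed chair stand and MDS-UPDRS motor scale, which are researcher-assessed, are marked at the same times.
- **Content of the resource-use item** (Follow-up assessment, economic data): the data are "collected using a tick box resource sheet aided by a resource use diary", with further resource use in the fall diaries. The listed items end with "GP and specialist appointments, physiotherapy, occupational therapy and admission to a care home will be identified and measured". The time taken to deliver PDSAFE is measured as a cost item of its own.
- **Contrast between arms** (Interventions): the programme "will consist of up to twelve, one hour face-to-face sessions with the physiotherapist" over six months. Controls have a single physiotherapist visit. Both arms continue usual care.
- **Protection of the blind** (Follow-up assessment): "Previous experience within the team suggests that participants may inadvertently unblind assessors". The stated measures are reminders before visits and a record of the assessor's guess of arm, with confidence in it, at the end of the trial.

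**The concern.** The plan treats unblinding as something a participant might let slip. Read together, these sections show a second route that the plan creates itself: the person who must not know the allocation is sent to collect an item that tracks it closely. A participant who answers the physiotherapy question fully and honestly may give the arm away without any slip.

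What is at stake is the credibility of the balance, chair-stand and motor results. Participants and therapists know the allocation, so these ratings depend on the assessor not knowing it. If the assessor does know, scores can drift towards the expected benefit, and no later analysis can remove that. The end-of-trial guess would show that unblinding had occurred, but not at which visit it arose, and it prevents nothing.

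**Working it through.** No figure in the plan is disputed. The check sets the sections side by side and then sizes the contrast between arms.

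**1. Does the blinded assessor collect resource use?** Follow-up assessment gives the Table 1 follow-up data to the blinded assessor's home visit. Table 1 marks resource use at 3, 6 and 12 months. No sentence gives the resource sheet to anyone else. The answer, as written, is yes. This does not depend on how far the face-to-face label in Table 1's method column extends down the rows.

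**2. Does resource use include physiotherapy?** Yes, it is named in the list of items.

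**3. How far apart are the arms?** Inputs are from the example delivery model in Interventions:

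- weeks 1–2, twice a week: 2 × 2 = 4
- weeks 3, 4 and 5, once a week: 3
- months 2 and 3, once each: 2
- months 4, 5 and 6, once each: 3

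Counted from the first session, the total is 4 + 3 + 2 = 9 by month 3 and 9 + 3 = 12 by month 6.

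Follow-up runs from randomisation, whereas Randomisation allows two weeks, and at most four, before the first visit. With that lag the month-3 and month-6 sessions can fall after the corresponding assessments, which gives 9 − 1 = 8 and 12 − 1 = 11.

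| | Intervention (example model) | Control (trial visit) |
|---|---|---|
| By the 3-month assessment | 8 to 9 | 1 |
| By the 6-month assessment | 11 to 12 | 1 |

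Usual-care physiotherapy may add to either column. The model is only an example and delivery is negotiated, so the intervention counts are illustrative.

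**4. How many ratings are exposed?** There are three researcher-assessed tests per visit. The answer depends on points the article does not state:

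- Trial sessions are kept off the sheet and are not mentioned: 0.
- Trial sessions are reported, and the sheet comes before the tests at months 3 and 6: 3 × 2 = 6 per participant.
- As above, and the same assessor returns at month 12: 3 × 3 = 9, the upper figure.
- Trial sessions are reported, but the tests come first at every visit: 0 if a different assessor attends each time. If the same assessor returns, 3 × 2 = 6, because what is learned at month 3 carries to months 6 and 12.

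**5. Does the stated protection reach this route?** A reminder asks participants not to volunteer their allocation. It cannot apply to a question that the assessor is required to ask. The recorded guess measures unblinding after the event.

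**The case against.** The strongest reply is that the article never says trial sessions go on the assessor's sheet. PDSAFE delivery time is costed separately, so physiotherapy in the list may well mean usual-care physiotherapy, which both arms may receive. The form is a tick box sheet with no stated count, controls also see a physiotherapist once, and a tick alone need not identify the arm. The list of items is not divided between the sheet, the resource diary and the posted fall diaries. The order of forms within the visit belongs in an assessor manual. The plan also acknowledges unblinding and intends to examine its extent.

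Much of this stands, and it rules out stronger readings that a reader might infer:

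- *That the schedule breaks the blind, or that the form reveals allocation.* The documents support only that it can. Exclusion of trial sessions is compatible with the text.
- *That all nine ratings per participant are exposed.* Treatment ends at about six months, so month 12 is reached only if knowledge carries over with a returning assessor, which is not stated.
- *That this is the only blinding in the trial.* Statistical analysis also provides for a blind review of the falling covariate and for subgroups fixed before unblinding.
- *That the main result is at risk through this route.* Falls come from self-report diaries returned by post.

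What does not stand is the argument that this is merely detail left to another document. The article positively assigns Table 1 data to the blinded assessor and names physiotherapy as a resource item. Excluding trial sessions would not settle the matter if the participant had to separate trial from usual-care physiotherapy aloud in front of the rater. Nor does the tick-box format settle it: Economic analysis attaches unit costs to all resource items, which needs quantities from some source, and a resource diary supports the sheet.

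**Conclusion.** The point holds as a design weakness that should be corrected. As written, the rater is assigned a required item that can disclose allocation at months 3 and 6, and at month 12 by carry-over. The contrast on the example model is roughly 8 to 12 physiotherapist sessions against one control visit. Between 0 and 9 ratings per participant could be affected, across three secondary outcomes.

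The conclusion rests on the assignment of Table 1 data to the blinded assessor, which is stated. Its size rests on whether trial sessions are reported on the sheet, on the order within the visit, and on whether the same assessor returns, none of which is stated. The direction and amount of any resulting bias cannot be estimated from the document.

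**What to change.** 1. State that trial physiotherapy contacts are not entered on the assessor's sheet. Take the number and length of PDSAFE and control visits from therapist records. This also prevents PDSAFE sessions from being counted twice, once as delivery cost and once as health-service physiotherapy.
2. Preferably, take the rest of the resource-use sheet out of the visit and return it in the pre-paid envelope with the monthly diary. The diaries already carry some resource use, and the trial co-ordinating centre, which already receives the allocation, can check the sheet.
3. At minimum, if the sheet stays in the visit, complete it only after the three rated tests are scored and closed. This protects that visit's ratings but not later ones if the same assessor returns.
4. Record the assessor's guess of arm and confidence at each visit, so that the timing of any unblinding can be seen.

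The cost is small: a change of route for one form, and wording in the protocol and assessor instructions. The downside is possibly somewhat more missing resource-use data than with face-to-face completion. The planned telephone reminders for late diaries and the multiple imputation planned for missing cost data address this in part.
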